**Secondary outcomes**	
Quantitative assessment of cartilage morphology	T2 mapping (MRI)
Molecular biomarkers of cartilage and bone turnover assessed in serum	Blood samples of venous blood to assess specific biomarkers: COMP and ARGS-aggrecan, NTX-I, TRAP5b and cytokines

SLHD = single-leg hop for distance, KOOS = knee osteoarthritis outcome score, ACL-RSI = ACL Return to Sport after Injury Scale, ACL-QoL = ACL Quality of Life, SACQ = Self-administered Comorbidity Questionnaire, PSS-10 = Perceived Stress Scale, MRI = magnetic resonance imaging, ARGS-aggrecan = ARGS neoepitope of aggrecan, COMP = Cartilage oligomeric matrix protein, NTX-I = N-terminal type I collagen cross-linked telopeptide, TRAP5b = tartrate-resistant acid phosphatase 5b.

a Data collection in Lund only.

The participants are told to wear shorts and t-shirt. Strength tests will be performed without shoes whereas the postural orientation tasks and hop tests will be performed with training shoes. In an effort to minimize bias related to learning effects of the injured leg, the right leg will be tested first (irrespective of whether the right or left leg is injured). This will be applied for all assessments except for isokinetic knee strength for which the non-injured leg will be tested first, according to the standard procedure for Biodex assessments.

### Predictors

2.3

#### Knee strength

2.3.1

Isokinetic concentric muscle strength tests during knee extension and flexion will be measured at 60°/sec with a dynamometer (Biodex Medical Systems, Shirley, New York). Four trial repetitions will be performed with submaximal effort, followed by a 1-min rest. Five test repetitions will then be performed and recorded. Peak torque (Nm) and normalized peak torque (Nm/kg) for knee extension and flexion will be recorded [29].

#### Hip and trunk strength

2.3.2

Isometric peak force (N) of hip external rotation, abduction, and extension, and trunk, will be measured with a hand held dynamometer (Power Track II Commander Echo; JTECH Medical, Salt Lake City, Utah, USA) as described [30]. During all assessments, a belt will be used to fixate the dynamometer and the participant will be encouraged to push against the dynamometer as much as they can. The leverage (m) will be measured from the joint axis of rotation to the point of application of the force transducer for each test. Each test will be repeated three times and each contraction will be maintained for 5 s with approximately 15 s of rest in between contractions. The peak value of the three trials in Newton meter, normalized for body weight (Nm/kg), will be used in the analysis.

#### Hop performance

2.3.3

Two reliable hop tests, the single-leg hop for distance and the side-hop, will be performed as described [31]. The participants will perform three to five practice trials followed by three maximum approved trials for the single-leg hop test for distance. The hop distance is measured in centimeters from the toe at the push-off to the heel at the landing position. The side hop will be performed once on each leg and the participants will be instructed to jump as many times as possible, landing outside two tape strips 40 cm apart, during a period of 30 s.

#### Postural orientation

2.3.4

The test battery consists of 5 functional tasks; single-limb mini squat (SLMS), stair descending (SD), forward lunge (FL), single-leg hop for distance (SLHD) and side hop (SH); tasks ranging from resembling daily to more demanding activities [32]. The tasks will be video-recorded from a frontal view for later assessment of the patient's postural orientation. The videos can be viewed several times and/or in slow motion if needed. Between 2 and 6 segment-specific postural orientation errors (POEs) will be observed and scored for each task on a 4-point ordinal scale from 0 to 3 where 0 = good postural orientation, i.e., represents no signs of POEs, 1 = “fair”, represents signs of POEs, 2 = “poor”, represents clear signs of POEs and 3 = “very poor”, represents when the execution of the test does not have any similarities to the intended task. The total POE score across all and within tasks and segment-specific POEs will be used in the analysis. High inter-rater reliability has been reported for this test battery in patients with ACL injury [32].

#### Patient-reported outcomes

2.3.5

Data for the following valid questionnaires will be collected and managed using an electronic data capture tool (REDCap) [33] (Lund) or using paper questionnaires (Oslo); The Short-Form 36 [34] will be used for assessment of perceived generic health. For patient-reported knee specific function, the KOOS (all subscales except pain) [35], Global knee function: Numeric Rating Scale (1–10 were 1 = worst and 10 = best) [36]and the ACL Quality of Life [37] will be used. The Tegner activity scale [38] will be used to assess pre-injury and current activity level and the ACL Return to Sport after Injury Scale [39] will be used to evaluate psychological readiness for returning to sport after injury. In addition, the participants will answer a questionnaire regarding their pre-injury activity, if they plan to return/have returned to the same activity or different activity level as well as time point of return (if any). Finally, the Perceived stress scale - 10 [40] will be used for perceived stress.

#### Muscle activation pattern

2.3.6

For the patients recruited in Lund, muscle activation patterns for the following muscles will be recorded during the landing phase of the single-leg hop for distance, using a wireless electromyographic system (Desktop DTS, Noraxon U.S.A. Inc, Scottdale, Arizona, USA); Gluteus maximus, Gluteus medius, Semitendinosus, Biceps femoris, Vastus medialis, Medial gastrocnemius and Iliocostalis. The maximum voluntary contraction (MVC) for each muscle will be calculated from the maximum value of three repetitions, synchronously collected with the torque data described above.

### Outcomes

2.4

#### Patient-reported outcome

2.4.1

The valid, patient-reported KOOS [35] subscale pain, scored on a 0 (worst) to 100 (best) scale will be used as a marker of symptomatic OA. In addition to the continuous measure of KOOS pain, a cut-off of will be used, where a score of ≤72 on the KOOS pain subscale will represent symptomatic knee OA and a score of >72 will represent no symptomatic knee OA, according to that previously described [9,10]. This particular cut-off is based on the normal mean (92.3 ± 10.0) KOOS pain score in an athletic population with a history of knee ligament injury and represents two standard deviations below the mean [41].

#### MR imaging

2.4.2

Compositional MRI of cartilage quality will be performed using T2 mapping using a 1.5 T scanner.

#### MR image acquisition

2.4.3

Subjects will be positioned in a supine position with their feet first in a 1.5 T MRI scanner (AvantoFit, Siemens Healthcare, Erlangen, Germany) and the injured knee placed in a knee coil (TxRx 15 Ch Knee, Siemens, Erlangen, Germany). After localizer sequences, four 2D proton density weighted turbo spin echo sequences will be acquired for scoring and clinical evaluation with: 1) sagittal orientation and no fat suppression, and 2–4) sagittal, transversal and coronal orientations with fat suppression. For T2 mapping, two sagittal slices positioned in the central part of each of the medial and lateral tibiofemoral cartilage compartments, respectively, will be acquired in a single, interleaved acquisition using a 2D multi echo spin echo sequence with 12 echoes. Finally, a sagittal T1 weighted 3D VIBE (Volumetric Interpolated Breath Hold Examination) sequence will be acquired for segmentation of the bone. Imaging parameters for each sequence are summarized in Table 3.

**Table 3 tbl3:** Image acquisition parameters for the proton-density weighted turbo-spin echo (PDW TSE), multi-echo spin echo (MESE) and T1 Weighted Volumetric Interpolated Breath Hold Examination (3D T1W VIBE) sequences.

Sequence	PDW TSE	PDW TSE	PDW TSE	PDW TSE	MESE	T1W VIBE
Orientation	Sagittal	Sagittal	Coronal	Transversal	Sagittal	Sagittal
2D/3D	2D	2D	2D	2D	2D	3D
Fat suppression	None	Fat Sat	Fat Sat	Fat Sat	None	Water excitation
Echo time (ms)	41	45	37	38	10–120	6
Repetition time (ms)^a^	3000	4550	3000	3760	2360	14
Flip angle						10
Turbo factor	10	11	5	5	12	
Field of view (mm^2^)	160×160	170×170	150×150	160×160	145×160	150×150
Voxel size (mm^3^)	0.4×0.4×3	0.5×0.5×3	0.5×0.5×3	0.5×0.5×3	0.4×0.4×3	0.3×0.3×0.6

a May vary slightly as the number of slices will be adjusted for coverage in each case.

#### Analysis and ROI definition

2.4.4

T2 maps will be calculated online at the scanner from the acquired multi echo spin echo images using a built-in application (MapIt). Using the ImageJ software (Rasband, W.S., ImageJ, U. S. National Institutes of Health, Bethesda, Maryland, USA, https://imagej.nih.gov/ij/, 1997–2018.), regions of interest (ROIs) will be defined covering the superficial half and the deep half of the cartilage in each of the medial and lateral weight-bearing femoral and tibial cartilages respectively, resulting in a total of eight ROIs per subject MR exam. Although the articular cartilage is generally divided into three layers, distinction beyond a superficial and deep ROI will not be possible here, due to the limited spatial resolution of the MR image. The femoral ROIs will cover a region from the middle of the tibial plateau (regarding anterior-posterior position) to the posterior horn of the meniscus. The tibial ROIs includes the central 1/3 of the tibial cartilage in the sagittal plane (Fig. 1). ROIs will be defined in the shortest TE (TE = 10 ms) image and the position of each ROI will then be copied to the corresponding T2 map for evaluation of T2.

#### Biomarker profiles

2.4.5

Blood samples of venous blood will be collected to assess molecular biomarkers of cartilage and bone turnover in serum [43]. Specific biomarkers including, but not limited to, cartilage markers cartilage oligomeric matrix protein (COMP; ELISA based immunoassay from BioVendor) and ARGS-aggrecan (ARGS neoepitope of aggrecan; in-house immunoassay based on Meso Scale Discovery platform (MSD)), and bone markers N-terminal type I collagen cross-linked telopeptide (NTX-I; ELISA based immunoassay from Osteomark) and tartrate-resistant acid phosphatase 5b (TRAP5b; ELISA based immunoassay from Quidel) will be analysed in batch mode [[44], [45], [46], [47]]. Possibly, inflammatory biomarkers (including C-reactive protein, tumour necrosis factor-α, interleukin-6; e.g. using MSD multiplex immunoassays) will be analysed in batch mode to obtain complementary data [48,49].

### Statistical analysis

2.5

For descriptive purposes, the mean (SD), or median (quartiles), at baseline and follow-up assessments will be used as appropriate. Separate linear regression models will be used to elucidate the influence of the absolute values of each predictor on the absolute value on primary, secondary and exploratory outcomes in cross-sectional analyses and on the absolute value as well as change in primary, secondary and exploratory outcomes in longitudinal analysis, adjusted for baseline values and possible confounders (e.g., age and associated injuries). In addition, logistic regression analysis will be used to elucidate the influence of each predictor on significant knee pain (KOOS pain ≤72 vs > 72). Assuming a clinically relevant correlation of 0.30 between knee extension strength and self-reported pain [50], we need 84 patients with 80% power at the 5% significance level. Based on this calculation, we will include 100 patients including an approximate drop-out of 15%. For explorative purposes, an analysis of covariance (ANCOVA) will be used to investigate differences in the presence of early knee OA between the 100 patients with ACLR and twenty sex and age matched non-injured individuals, adjusting for activity level.

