**Methods and analysis:**

In this prospective cohort study, 100 patients (50% women, 18–35 years) with ACLR will be recruited from Skåne University Hospital, Sweden and Oslo University Hospital, Norway. They will be assessed with a comprehensive test battery of muscle function including muscle strength, muscle activation, hop performance, and postural orientation as well as patient-reported outcomes, one year (baseline) and three years (follow-up) after ACLR. Primary predictor will be knee extension strength, primary outcome will be patient-reported knee pain (Knee injury and Osteoarthritis Outcome Score, subscale pain) and secondary outcomes include compositional MRI (T2 mapping) and turnover of cartilage and bone biomarkers. Separate linear regression model will be used to elucidate the influence of each baseline muscle function variable on the outcomes at follow-up, adjusted for baseline values. Twenty non-injured individuals will also be assessed with MRI. This study is approved by The Regional Ethical Review Board in Lund (Sweden) and Oslo (Norway).

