Knee joint load is suggested to be a contributing factor for knee OA development and progression [[22], [23], [24], [25]]. Sensorimotor function, such as muscle strength and muscle activation patterns, factors that are modifiable by training, influences the magnitude of joint load and may, thus, play an important role for the onset of knee OA [26]. Knee muscle weakness has been reported to be associated with an increased risk of developing radiographic and symptomatic knee OA in individuals without previous knee joint injury [27], whereas the evidence for such association in individuals with a knee injury is inconclusive [27,28]. A recent systematic review reported conflicting results of other measures of muscle function than knee muscle strength, such as hop performance, as contributing factors for radiographic or symptomatic OA development after knee injury [28]. Furthermore, low patient-reported function 2 years after ACLR has also shown to be associated with symptomatic and radiographic knee OA ten years post injury [28]. To our knowledge, there are no studies on the role of muscle function as a possible modifiable protective mechanism for the development of early-stage OA after knee injury, using a comprehensive test battery of muscle function as well as different measures of early knee OA. Such knowledge would help in designing more effective training interventions in the treatment of knee injury and subsequent early-onset OA. Thus, the aim of this prospective cohort study including young people with anterior cruciate ligament reconstruction (ACLR) is to study the association between different measures of muscle function and early future knee OA assessed as patient-reported pain, features indicative of early radiographic OA measured with MRI, and early detection of OA in biomarker profiles, respectively. In addition, we will investigate the prevalence of early knee OA in individuals 1 and 3 years post ACLR, respectively, compared to non-injured controls.

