### Participant and setting

2.1

Patients will be consecutively recruited from the Department of Orthopedics, Skåne University Hospital, Sweden (main site) and the Department of Orthopedics, Oslo University Hospital, Oslo, Norway. The majority of patients (approx. 70%) will be included in Sweden. The study is approved by The Regional Ethical Review Board in Lund, Sweden (Dnr 2016/319) and Oslo, Norway (REK sør-øst D: 2016/1128).

*Inclusion criteria*: i) one year (between 10 and 16 month) after ACLR, with or without associated injuries to other structures of the knee (e.g., collateral ligament(s), meniscal injury), ii) age 18–35 years. *Exclusion criteria*: i) previous serious injury or surgery to either knee (e.g., ACL tear, meniscal tear), ii) diseases or disorders overriding the knee condition (e.g., neurological disease), iii) contra-indicators for MRI, iv) not understanding the languages of interest (any Scandinavian language or English). Possible confounders to record at the assessments include: i) additional surgery to the index knee between the time point of ACLR and inclusion and/or during follow-up, ii) serious injury to the index knee (e.g., giving-way episode(s)) resulting in pain and/or swelling and requiring inpatient or outpatient health care between the time point of ACLR and inclusion and/or during follow-up. Demographics (e.g., age sex, BMI, heredity) and other patient-reported outcomes will be collected at baseline and at follow-up (See Table 1 for full details). As a sample of convenience, 20 age- and sex-matched non-knee injured individuals will be recruited among students in Lund, Sweden. With the exception that these individuals should be free from ACL injuries to both knees, the inclusion/exclusion criteria will be the same for this cohort as for the patient cohort.

**Table 1 tbl1:** Demographics and patient-reported outcomes to be collected at baseline and at follow-up.

	Baseline		Follow-up	
	ACLR patients	Controls	ACLR patients	Controls

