### Assessments

2.2

All predictors and outcomes will be assessed at 1 year (baseline) and at 3 years (follow-up) after ACLR. *Primary predictor* is knee extension muscle strength at baseline. *Secondary predictors* are knee flexion, hip, and trunk muscle strength, hop performance, postural orientation and patient-reported outcomes (except patient-reported pain) at baseline. *Exploratory predictor* is muscle activation pattern at baseline. *Main outcome* is the Knee injury and Osteoarthritis Outcomes Score (KOOS), subscale pain at follow-up. *Secondary outcome* is T2 (MRI) and biomarker profiles at follow-up (full description of predictors and outcomes are outlined below and in Table 1, Table 2). One physical therapist researcher will perform all functional assessments in Lund and another physical therapist researcher will perform all functional assessments in Oslo. The researchers will give standardized verbal instructions and an inter-rater reliability testing has been performed, showing moderate to excellent inter-rater reliability for all functional assessments (ICC_2*K*_ 0.66–1.0) (See Appendix A for detailed description of the reliability assessment).

**Table 2 tbl2:** Predictors and outcomes at baseline and follow up.

Predictors at baseline and follow-up for ACLR patients	Data collection instrument

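### The supplementary logistic analysis of KOOS pain ≤72 states neither a baseline adjustment nor a time point, so a strength-pain association already present at 1 year can look like protection against future symptomatic OA

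*Protocol article*

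**What the plan says.** The aim in the Introduction is the association of muscle function with "early future knee OA assessed as patient-reported pain", alongside MRI and biomarker measures. Section 2.4.1 adds a binary version of the pain outcome, in which "a score of ≤72 on the KOOS pain subscale will represent symptomatic knee OA". Section 2.2 fixes the visits: "All predictors and outcomes will be assessed at 1 year (baseline) and at 3 years (follow-up) after ACLR".

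Section 2.5 gives covariates model by model:

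- The linear models are "adjusted for baseline values and possible confounders (e.g., age and associated injuries"). The abstract likewise ties its baseline adjustment to linear regression: "influence of each baseline muscle function variable on the outcomes at follow-up, adjusted for baseline values".
- The logistic model is introduced in the next sentence: "logistic regression analysis will be used to elucidate the influence of each predictor on significant knee pain (KOOS pain ≤72 vs > 72"). It has no covariates, no time point and no restriction to patients above the cut-off at baseline.
- The exploratory ANCOVA against controls names its own covariate, activity level.

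Section 2.1 lists four exclusion criteria. One is "previous serious injury or surgery to either knee (e.g., ACL tear, meniscal tear"); the others concern overriding disease, MRI contraindications and language. None concerns the level of knee pain at inclusion.

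**The concern.** Under the article's own definition, a patient at or below 72 at 1 year already has symptomatic OA. Nothing keeps such a patient out of the cohort or apart in the logistic analysis. Someone who scores 65 at both visits would count as a 3-year case whose status is attributed to 1-year strength.

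Strength and pain are measured at the same baseline visit, and a painful knee may test weaker. Baseline pain can also be expected to predict 3-year pain. If baseline pain is left out of the model, it can link strength to 3-year case status even when strength adds nothing to the prediction of later pain. The error points towards strength looking protective, which is the conclusion the Discussion hopes to draw for screening and treatment.

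**Working it through.** **The plan's own figure.** The sample size is for a correlation of 0.30, with 80% power at 5% (two-sided assumed). Fisher's z gives n = ((1.960 + 0.842)/atanh(0.30))² + 3 = (2.802/0.3095)² + 3 = 84.9. With the small-sample bias correction, n = 84 has 80.0% power, so the stated 84 reproduces. Dropout: 84/0.85 = 98.8, and 100 × 0.85 = 85 completers. This calculation covers the continuous correlation. No size or power is stated for the logistic analysis.

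**Inputs for the check.**

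- From the article: cut-off 72; 85 completers; a reference KOOS pain distribution, the "normal mean (92.3 ± 10.0) KOOS pain score in an athletic population with a history of knee ligament injury". That is a reference population, not this cohort.
- Borrowed from the article: a correlation of 0.30 between strength and 1-year KOOS pain. The article uses 0.30 for sample size and does not call it cross-sectional, so using it this way is an assumption.
- Assumed: 1-year to 3-year KOOS pain correlation ρ of 0.4, 0.6 or 0.8; two cohorts with more pain (mean 85 or 80, SD 13); the same mean and SD at both visits; normality, ignoring the ceiling at 100, which does not change who is ≤72.

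**Model.** In SD units, with e₁ and e₂ independent standard normal:

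- 1-year pain score = 0.30 × strength + √(1 − 0.30²) × e₁
- 3-year pain score = ρ × 1-year score + √(1 − ρ²) × e₂

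Strength therefore has no effect on the 3-year score once the 1-year score is known. A correct longitudinal analysis should give an odds ratio of 1. Logistic models for ≤72 at 3 years were fitted on 400,000 draws per scenario.

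**Expected cases.** The proportion ≤72 is Φ((72 − mean)/SD):

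- 92.3, SD 10: Φ(−2.03) = 2.1%, and 85 × 0.021 = 1.8 cases
- 85, SD 13: Φ(−1.00) = 15.9%, 13.5 cases
- 80, SD 13: Φ(−0.615) = 26.9%, about 23 cases

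**Results** (odds ratio per SD of strength; values in the order ρ = 0.4 / 0.6 / 0.8):

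| Mean, SD | Unadjusted | Adjusted for 1-year score | Only patients >72 at 1 year, unadjusted | 3-year cases already ≤72 at 1 year | New cases per 85 |
|---|---|---|---|---|---|
| 92.3, 10 | 0.74 / 0.64 / 0.54 | 1.00 / 1.01 / 0.98 | 0.77 / 0.70 / 0.62 | 12% / 25% / 43% | 1.6 / 1.3 / 1.0 |
| 85, 13 | 0.80 / 0.72 / 0.64 | 0.99 / 1.00 / 1.00 | 0.86 / 0.82 / 0.75 | 34% / 46% / 61% | 8.9 / 7.3 / 5.2 |
| 80, 13 | 0.82 / 0.74 / 0.66 | 1.00 / 1.00 / 1.00 | 0.90 / 0.85 / 0.80 | 45% / 55% / 69% | 12.7 / 10.2 / 7.2 |

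Dropping baseline cases does not cure the problem (0.62 to 0.90). Among those above 72, a lower 1-year score still goes with weaker strength and with a higher chance of crossing the cut-off. The continuous baseline score does cure it.

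**What 85 patients would show.** A rough standard error of the log odds ratio per SD is 1/√(85 × p × (1 − p)): 0.75, 0.30 and 0.24 for the three cohorts. Taking |log OR|/SE against 1.96, the artefact alone would reach p < 0.05 in about 7% to 13%, 12% to 32% and 13% to 40% of studies, against a nominal 5%. For example, at mean 85 and ρ = 0.6: 0.329/0.297 = 1.11, which gives about 20%. With about 2 events the first range is only indicative.

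**The case against.** The strongest reply is that this is brevity, not a choice. The logistic sentence opens as an addition to the linear one, uses the same predictors, and omits confounders and time point as well; the adjustment may be meant to carry over. That reading is possible, and the text is better called ambiguous than wrong. It is not the natural reading, because the linear models and the ANCOVA each name their own covariates and the abstract attaches baseline adjustment to linear regression. The linear sentence also covers both cross-sectional and longitudinal analyses, so what would carry over is unclear. For a cross-sectional analysis, existing cases are the right outcome.

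Three further points stand. The cut-off supplements the continuous primary analysis, which is baseline-adjusted. An unadjusted association with 3-year status is a legitimate quantity for screening, and the article also plans to report prevalence at 1 and 3 years. At the article's reference mean and SD, with about 2 events, the artefact would rarely reach significance and the model could barely be fitted; it becomes material only in the assumed cohorts with more pain.

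A reader might infer that the analysis measures persisting pain instead of onset. The documents do not support that. They never say outright that baseline cases are counted; this follows only from the lack of a restriction. At the reference mean and SD, 57% to 88% of 3-year cases would be new.

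**Conclusion.** The point holds for the longitudinal use of the supplementary logistic analysis. As written, that analysis has no stated baseline term, no time point and no separation of new from persisting cases, so an association already present at 1 year can pass for prediction of future symptomatic OA. With no effect of strength given 1-year pain, the unadjusted odds ratio per SD is about 0.54 to 0.82; adjusting for the continuous 1-year score returns it to about 1.0. The direction is the same in every scenario tried. The size depends on the borrowed 0.30, the assumed correlation between visits and the assumed cohort mean and SD, none of which the article gives for this cohort.

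It would go too far to infer that the study's main conclusion is compromised: KOOS pain at follow-up, analysed continuously with baseline adjustment, is untouched. The change is worth making because the covariate is already collected and the linear models already use it.

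**What to change.** In section 2.5, state that the longitudinal logistic outcome is KOOS pain ≤72 at 3 years and that the model includes 1-year KOOS pain as a continuous covariate. If a cross-sectional logistic analysis is also intended, name it separately. Do not rely on restricting to patients above 72 at baseline in place of the covariate.

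Report descriptively how many 3-year cases were already ≤72 at 1 year and how many are new, and do not describe the combined outcome as onset or development.

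The cost is a sentence or two; no new data are needed. The real downside is one more parameter with few events: about 2 among 85 completers at the reference mean and SD, and about 13 to 23 in the assumed cohorts with more pain. It is sensible to say in advance that a penalised model, or description alone, will be used if events are too few. Sparse events are not a reason to leave out the baseline score.

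### The supplementary logistic models for KOOS pain ≤72 have no planned event count, and at the reference mean and SD that the article cites only about 2–5 of 85 completers would be events

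*Protocol article*

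**What the plan says.** Section 2.4.1 (Patient-reported outcome) describes the KOOS pain subscale as "scored on a 0 (worst) to 100 (best) scale" and adds a binary version, with 72 or below taken as symptomatic knee OA. On the origin of the threshold it says: "This particular cut-off is based on the normal mean (92.3 ± 10.0) KOOS pain score in an athletic population with a history of knee ligament injury". Its position relative to that reference is given in the same sentence: it "represents two standard deviations below the mean [41" (the last figure is a citation number).

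Section 2.5 (Statistical analysis) first sets out linear regression of the continuous outcomes, "adjusted for baseline values and possible confounders (e.g., age and associated injuries". It then adds that "logistic regression analysis will be used to elucidate the influence of each predictor on significant knee pain (KOOS pain ≤72 vs > 72". The adjustment wording is not repeated for the logistic models.

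The sample size in the same section rests on the continuous score. Its premise reads "Assuming a clinically relevant correlation of 0.30 between knee extension strength and self-reported pain". The resulting requirement is stated as "we need 84 patients with 80% power at the 5% significance level". For enrolment the article says "we will include 100 patients including an approximate drop-out of 15" per cent. The article gives no expected number or proportion of patients at or below 72, and no sample-size basis for the logistic models.

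**The concern.** A threshold two standard deviations below a mean cuts off a small tail of the population that supplied the mean. That reference population already had knee ligament injury, so it is a natural first guide to patients after ACL reconstruction. If this cohort resembles it, each logistic model has only a few events, and it is to be fitted separately for every strength, hop, postural and questionnaire predictor.

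With few events, maximum-likelihood odds ratios are imprecise and on average too far from 1. Repeating the fit over many predictors makes it more likely that some extreme value appears. The Discussion defends 72 as the chosen marker of early symptomatic OA and looks ahead to screening by muscle function, so the binary results may well be quoted.

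**Working it through.** **Inputs.** Section 2.4.1: reference mean 92.3, SD 10.0, cut-off 72, scale 0–100. Section 2.5: r = 0.30, 80% power, 5% level, 84 needed, 100 enrolled, about 15% drop-out. Not in the article, so assumed and varied: the cohort's KOOS pain distribution and the true effects.

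**The plan's own figure.** Fisher's z, two-sided: n = ((1.960 + 0.842)/atanh(0.30))² + 3 = 84.9. With the bias-corrected form, power at n = 84 is 80.0%. The stated 84 is therefore reproduced. Completers: 100 × 0.85 = 85. Nothing in this calculation concerns events.

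**Events at the reference mean and SD.**
- Normal: z = (72 − 92.3)/10 = −2.03, so P = 2.1%, and 85 × 0.0212 = 1.8 events. The chance of no event at all is about 16%.
- Bounded and skewed (beta on 0–100, same mean and SD): a + b = 0.923 × 0.077/0.10² − 1 = 6.107, so a = 5.64 and b = 0.47. P = 5.5%, and 85 × 0.0549 = 4.7 events. The chance of fewer than 10 events is 98%.
- Any shape with this mean and SD (Cantelli bound): P ≤ 100/(100 + 20.3²) = 19.5%, so at most 16.6 events.

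**Events if the cohort is worse (assumed values).**

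| Mean, SD | Events in 85, normal | Events in 85, beta |
|---|---|---|
| 90, 10 | 3.1 | 5.6 |
| 88, 12 | 7.8 | 9.3 |
| 85, 12 | 11.8 | 12.2 |
| 82, 15 | 21.5 | 19.0 |

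**Maximum-likelihood fits with the predictor alone.** Simulation with n = 85, true odds ratio 0.6 per SD (log odds ratio −0.511), 2,000 data sets per rate. Inflation is the mean log odds ratio among estimable fits divided by −0.511, minus 1. The interval ratio is upper limit over lower limit, exp(2 × 1.96 × median SE).

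| Event rate | No events | Separated | Inflation | Interval ratio | Power |
|---|---|---|---|---|---|
| 2.1% | 16.8% | 1.3% | 26% | 23.7 | 6% |
| 5.5% | 1.1% | 0.3% | 11% | 7.6 | 15% |
| 10% | 0% | 0% | 10% | 4.7 | 27% |
| 15% | 0% | 0% | 8% | 3.7 | 36% |

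**Maximum-likelihood fits with four covariates** (predictor, baseline pain, age, associated injury; coefficients assumed, same true odds ratio for the predictor).

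| Event rate | No events | Separated or not converged | Inflation |
|---|---|---|---|
| 2.1% | 15.6% | 51.9% | 20% |
| 5% | 1.5% | 23.6% | 38% |
| 10% | 0% | 3.6% | 27% |
| 15% | 0% | 0.2% | 15% |

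The first two columns are disjoint. At 2.1%, 15.6 + 51.9 = 67.5% of data sets give no usable estimate; at 5%, 1.5 + 23.6 = 25.1%.

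**Effect of the remedy.** In a further simulation with one or two covariates, maximum likelihood inflated the log odds ratio by about 6–17% at event rates of 2–15% and failed in about 20% of samples at 2.1%. Firth's penalty removed most of the bias at 5.5% and above, shrank toward the null at 2.1%, and lowered the root mean square error at every rate. The size of the inflation depends on the assumed coefficients and differs between these runs; its direction, away from the null, does not.

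**The case against.** The strongest objection is that the cut-off fixes a tail in a reference athletic population, not in this cohort. Section 2.1 enrols patients 10–16 months after reconstruction, allows associated injuries, records further surgery and re-injury, and does not require athletic participation. A modestly worse distribution gives 8–12 events. This stands: a reader might infer that a handful of events is certain by definition, and the article does not support that.

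Second, a reader might infer that separation will be common in these models. It is common only in the four-covariate version at event rates of about 5% or less. Section 2.5 does not state that covariate set for the logistic models, and with the predictor alone separation is about 1% or lower. This stands too.

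Third, a reader might infer that pain already present at one year will be reported as newly developed OA, because the logistic sentence is silent on baseline. The article does not say so: the outcome there is called significant knee pain, and the sentence follows directly on one that adjusts for baseline. This harm and the many-covariate harm also belong to different readings of the sentence, so they cannot both apply in full.

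Fourth, the article names neither an estimator nor an interval method, and such detail may sit in a fuller plan. That is fair, and the missing detail is not the point here. What the article does fix (the cut-off, a logistic model for each predictor, and a sample size for a continuous correlation) fits together poorly at the only distribution it cites.

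Finally, the logistic models are supplementary, and conclusions already rest on continuous KOOS pain. That is correct and limits the importance of the point.

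**Conclusion.** The concern holds in a limited form. At the only mean and SD given, about 2–5 of 85 completers would score 72 or below; under the assumed worse distributions the count is roughly 3–21. At the low end, single-predictor intervals span a factor of about 8 to 24 from lower to upper limit, power is 6–15% for an odds ratio of 0.6 per SD, and log odds ratios are inflated by 11–26% among estimable fits. If four covariates are used, inflation is still 15–27% at event rates of 10–15%, although separation is then rare (3.6% or less).

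These results assume 85 completers, fitting by maximum likelihood, and the stated effect sizes; the cohort's event rate is unknown. A reader might infer that the main result is at risk. It is not: the primary linear regression of continuous KOOS pain and its sample size do not depend on the cut-off.

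**What to change.** In section 2.5, specify for KOOS pain ≤72 at follow-up:
- Firth-penalised logistic regression containing the predictor and continuous baseline KOOS pain only, with profile-penalised likelihood confidence intervals;
- the number of patients at or below 72, reported beside every odds ratio;
- a minimum event count, fixed before follow-up data are examined, below which counts with exact intervals are given and no per-predictor odds ratios.

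The minimum is a matter of judgement. A limit of ten, for example, would withhold odds ratios with probability 98% at a 5.5% event rate, 66% at 10% and 16% at 15%.

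Naming baseline KOOS pain also settles whether the logistic models are adjusted. The change is to analysis wording only and needs no further patients or data. The price is slight shrinkage toward the null, more marked at the lowest event rates, and fewer confounders in this supplementary model.
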